### Sub-study 2: patients *without* clinically significant depressive symptoms

This sub-study involves a sample of approximately 300 patients whose baseline PHQ-9 scores were less than 5. The aims of this sub-study are:

(1) To examine whether the interventions are associated with (a) detrimental *process of care* effects (including unnecessary initial antidepressant prescriptions, physician rating of greater effort during visit, longer visit duration), and/or (b) decrements in patient functioning (specifically, worse physical health at 12 week follow-up). It is hypothesized that the active interventions will not result in detrimental outcomes in those without evidence of significant depression.

(2) To examine whether the interventions may lessen perceived depression stigma among non-depressed persons. It is hypothesized that the active interventions will result in reduced stigma after the index visit among patients without evidence of significant depression.

### Measures

Data are obtained from patient questionnaires, physician questionnaire after completed encounter, and encounter chart review. For several measures, similar information is gathered from all three sources. Literature on agreement among these three sources of information in a variety of settings typically suggests only modest agreement [67-70]. For most assessments, the primary measurement source will be considered patient report, which may be more closely associated with outcomes [68]. Based on the theoretical framework of the intervention, the effects of the intervention will depend on the extent to which patients perceive (and recall) specific aspects of encounters. Thus, even if the physician correctly recalls an aspect of the encounter (for example a recommendation for treatment), it is still critical for that recommendation to be perceived by the patient as sufficiently salient to result in patient recall of the recommendation. Chart documentation presumably reflects issues thought important enough by the doctor to document in the chart. But again, unless those issues are effectively communicated to the patient they are less likely to affect patient recall.

The outcome measures, measurement points, and assessment methods for the two sub-studies are summarized in Table 1. When a construct is also measured at baseline (pre-intervention), the same variable definitions are used.

**Table 1 T1:** RCT Sub-studies and Process and Outcome Measures

	**Measurement points**		**Method(s) of measurement**
	**Immediately after index office visit**	**12 week follow-up**	

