### Sub-study 1: patients *with* clinically significant depressive symptoms

This sub-study involves a sample of approximately 500 patients with a Patient Health Questionnaire-9 (PHQ-9) score of ≥ 5 (mild or greater depressive symptoms) on the previsit survey.

**Key Outcome: Initial Depression Care** The key process of care measure is a composite outcome termed *Components of Initial Depression Care (CIDC).* CIDC is coded positive if an antidepressant prescription or mental health referral is provided at the index study visit among the subset of participants with a high likelihood of clinically significant depression (defined as a baseline PHQ-9 score ≥ 10). This outcome is defined as “key” based on the primary study goal, which is to increase patient engagement in care at the initial visit. For patients with clinically significant depression, evidence supports the use of antidepressants and/or psychotherapy or counseling [58-60], and the study was powered to detect a significant intervention effect on this outcome. It is hypothesized that the active interventions will result in a greater likelihood that physicians will offer and patients will accept these treatments.

**Other outcomes** Other outcomes pertinent to Sub-study 1 include effects of the two active interventions on primary care follow-up interval; self-reported physical and mental health at 12 weeks; patient engagement with care during and immediately after the index visit and patient self-efficacy for communication immediately after the index visit; depression-related stigma immediately after the index visit and at 12 weeks; and suicide inquiry by the physician during the index visit.

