**Sub-study 1: patients*****with*****clinically significant depressive symptoms (baseline PHQ-9 ≥ 5)**			
Process of care			
Key outcome - components of initial depression care (CIDC): antidepressant prescription and/or mental health referral among participants with baseline PHQ-9 ≥ 10*	X		PQ, PCPQ, MRR
Others			
Antidepressant prescription and/or mental health referral among all sub-study participants*	X		
Follow-up with PCP at an appropriate interval†	X		
Inquiry regarding self-harm/suicidal thoughts	X		
Patient function			
PHQ-8^‡^ score	X	X	PQ
SF-12 Mental Component Summary score		X	
SF-12 Physical Component Summary score		X	
Patient engagement in depression care			
Readiness			PQ
To discuss depression (in general) with PCP	X		
To discuss depression treatment with PCP	X		
Self-efficacy			
For recognizing depression	X	X	
For discussing depression with PCP	X	X	
Provider-patient interaction			PQ, PCPQ, MRR
Discussion of depression	X		
Patient request for depression treatment	X		
Patient perceived depression stigma	X	X	PQ

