**Sub-study 2: patients*****without*****clinically significant depressive symptoms (baseline PHQ-9 < 5)**			
Process of care			
Antidepressant prescription (over-treatment)	X		PQ, PCPQ, MRR
Distraction effects			
Index office visit length	X		
Patient request for depression treatment	X		
Physician visit effort	X		
Patient function			
SF-12 Physical Component Summary score (potential toxicity, i.e. reduced function)		X	PQ
Patient perceived depression stigma (potential reduction)	X	X	PQ

* Sub-study 1 primarily powered to examine this outcome; research evidence indicates PHQ-9 scores ≥ 10 are associated with significant life impairment (e.g. reduced functional abilities) and a strong likelihood of clinical depression, while scores of 5–9 are more equivocal in this regard.

^†^ Not an evidence-based element of care, but endorsed in prevailing clinical practice guidelines.

^‡^ Includes all PHQ-9 items except the item concerning self-harm thoughts.

Abbreviations:

*AMEP2*, Activating Messages for Enhancing Primary Care Practice; *MRR*, medical record review; *NA*, not applicable (participants in this sub-study are not followed up); *PCP*, primary care provider; *PCPQ*, PCP questionnaire; *PHQ*, Patient Health Questionnaire; *PQ*, patient questionnaire.

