### Procedures for post-visit assessments

Immediately following the office visit, subjects returned to the tablet PC to complete a post-visit questionnaire, which contained many of the same items as on the pre-visit questionnaire plus questions about the encounter (e.g., whether they asked about depression and/or depression-related care and whether the physician prescribed an antidepressant, made a mental health referral, or arranged for follow-up). Twelve weeks after the index visit, RAs telephoned patients reporting PHQ-8 scores of ≥ 5 *either* during screening *or* on the day of the index visit to assess treatment adherence, severity of depressive symptoms, and health status using a scripted follow-up interview.

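### Patient report is the default primary source, with no stated exception for antidepressant overtreatment or CIDC, both of which are physician actions; for overtreatment the recall rationale does not fit and under-reporting weakens the noninferiority test

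*Protocol article*

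**What the plan says.** The article's Measures section describes three sources: patient questionnaire, physician questionnaire and chart review. On their concordance it says "Literature on agreement among these three sources of information in a variety of settings typically suggests only modest agreement [67-70". It then sets the default: "For most assessments, the primary measurement source will be considered patient report, which may be more closely associated with outcomes [68". The reason given is that "the effects of the intervention will depend on the extent to which patients perceive (and recall) specific aspects of encounters", and the example used is a physician's recommendation for treatment.

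The key outcome is worded as something the physician does: "CIDC is coded positive if an antidepressant prescription or mental health referral is provided at the index study visit". Table 1 lists all three sources for CIDC ("antidepressant prescription and/or mental health referral among participants with baseline PHQ-9 ≥ 10") and for the Sub-study 2 harm outcome ("Antidepressant prescription (over-treatment"). It names none of them as primary for either outcome. The post-visit section says that patients were asked "whether the physician prescribed an antidepressant, made a mental health referral, or arranged for follow-up", and that this was done at once: "Immediately following the office visit, subjects returned to the tablet PC to complete a post-visit questionnaire".

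Sub-study 2 tests prescribing for noninferiority, combined PSA/IMCP against control. The absolute margin is 3.5 percentage points, one-sided at 5%, by the Farrington-Manning method (Power calculations and sample size; Planned analytic approach).

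**The concern.** Care that was provided and care that the patient recalls are different outcomes. The default source measures the second, while the CIDC definition and the overtreatment aim describe the first.

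For overtreatment the stated rationale fails. It may be reasonable to say that a recommendation matters only if the patient takes it in. An unnecessary antidepressant is a harm whether or not the patient knows what it is. Prescriptions that patients miss lower both risks and the difference between them. Against a fixed absolute margin this favours a conclusion of safety, even when patients in all arms miss the same share.

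For CIDC, the PSA was designed to encourage requests for an antidepressant or a referral, and the control video was about sleep hygiene. If that exposure changes how accurately patients report these acts, a patient-reported difference mixes changed care with changed recognition.

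**Working it through.** **The plan's own figure.** Inputs from the power section: 204 active, 102 control, risk 1% in every arm, margin 3.5 points, one-sided 5%. The asymptotic Farrington-Manning power is 80.8%, which reproduces the stated 80%. Exact enumeration of the same test gives 85.6%.

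**Overtreatment with under-reporting.** Table 2 gives PHQ-9 < 5 counts of 90 (IMCP), 109 (PSA) and 109 (control), so active is 90 + 109 = 199 and control is 109. True risks are set at the margin: 1.0% control and 1.0 + 3.5 = 4.5% active. The documents give no sensitivity *s* for patient report, so it is assumed, equal in all arms, with no false positives.

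Observed risks are 4.5%×*s* and 1.0%×*s*; the observed difference is 3.5×*s* points. The chance of declaring noninferiority is the sum of exact binomial probabilities over all outcomes where the score statistic is below −1.645.

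| *s* (assumed) | Observed risks | Difference (points) | False noninferiority, 199 vs 109 | Same, planned 204 vs 102 |
|---|---|---|---|---|
| 1.0 | 4.50% vs 1.00% | 3.50 | 4.3% | 5.6% |
| 0.9 | 4.05% vs 0.90% | 3.15 | 6.1% | 8.2% |
| 0.8 | 3.60% vs 0.80% | 2.80 | 8.7% | 11.8% |
| 0.6 | 2.70% vs 0.60% | 2.10 | 18.3% | 23.4% |

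**Overtreatment with false positives as well.** Assume sensitivity 85% active and 75% control, specificity 95% in both:
- Active: 0.045×0.85 + 0.955×0.05 = 8.60%.
- Control: 0.010×0.75 + 0.990×0.05 = 5.70%.
- Difference 2.90 points; false noninferiority 7.6%.

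If active specificity is 92% instead:
- Active: 0.045×0.85 + 0.955×0.08 = 11.47%.
- Difference 5.77 points; false noninferiority 0.9%. The direction has reversed.

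**CIDC with no true effect.** Assume a true rate of 35% in both arms, sensitivity 85% active and 75% control, specificity 95% in both:
- Active: 0.35×0.85 + 0.65×0.05 = 33.0%.
- Control: 0.35×0.75 + 0.65×0.05 = 29.5%.
- Spurious difference 3.5 points, against the 15 points the sub-study was designed to detect.

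Table 2 gives 66 + 39 = 105 IMCP and 56 + 33 = 89 control patients with PHQ-9 ≥ 10. At these sizes the standard error is √(0.330×0.670/105 + 0.295×0.705/89) = 6.67 points, and two-sided rejection rises from 5% to about 8%.

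**CIDC with equal accuracy in both arms.** The observed difference is the true difference × (sensitivity + specificity − 1). At an assumed 0.80 and 0.95, a true 15 points becomes 15×0.75 = 11.25 points. Non-differential error dilutes the effect.

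**The case against.** The strongest reply is that the default covers most assessments, not all. Some Table 1 items, such as physician visit effort, are plainly not patient-reported, so unlisted exceptions exist, and a condensed article may leave the per-outcome rule to a fuller document. This stands in part. A reader might infer that the plan definitely assigns patient report to both outcomes; the text does not say so. It does give a general rule, argues it with a treatment recommendation, and states no exception for the two outcomes where the source matters most.

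Second, patient report is an argued choice. The study aims at patient engagement, and the CIDC hypothesis includes patients accepting treatment. For CIDC this carries weight, and a simple replacement by the chart would be a trade-off. It does not carry over to overtreatment.

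Third, the contrast in priming is limited. All arms answered the same questions on visit agenda, treatment preferences and stigma before viewing anything, and all had been asked about current antidepressant use. Reports were collected straight after the visit. A reader might infer that CIDC is inflated; the documents show only that it could be, if accuracy differs by arm.

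Fourth, a reader might infer that the overtreatment error always favours safety, or that it is large. Neither is supported. Extra active-arm false positives reverse it, and the 18.3% figure needs recognition of only 60%, which nothing in the article supports.

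Finally, the other sources have faults. The safety plan says physicians were reminded of the intervention content, so their form is not masked. Chart documentation may also differ by arm if an activated patient raises depression.

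**Conclusion.** The point holds in a limited form. For Sub-study 2 antidepressant prescribing, patient report is a poor default: its rationale does not apply to a harm, and equal under-reporting alone makes the noninferiority test anti-conservative. At the accrued sizes, false noninferiority rises from 4.3% to 6.1–8.7% for sensitivities of 0.9–0.8, and to 18.3% at 0.6. This rests on assumed sensitivities, true risks exactly at the margin, and no excess of false positives in the active arms.

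The CIDC part is weaker. A bias in favour of the interventions needs accuracy that differs by arm; the illustrative size is 3.5 points against 15. Equal error would work against the interventions. What is established for CIDC is a mismatch between an outcome defined as care provided and a default source that measures care perceived.

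**What to change.** For Sub-study 2 antidepressant prescribing, make the index-visit medical record the primary source, abstracted without knowledge of arm. Count events reported on the physician form as well, and give patient report as a sensitivity analysis.

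For CIDC, patient report may stay if the investigators wish, but label it patient-perceived care. Prespecify a chart-based CIDC, abstracted without knowledge of arm, as a companion analysis. Require the two to agree before concluding that the care provided has changed, and report each source separately.

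The cost is mainly wording, since all three sources are already collected. The chart will miss undocumented care, chiefly informal referrals. The physician form is not masked, and documentation may itself vary by arm; separate reporting by source would let readers see whether the conclusion depends on this.

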**Sub-study 1: patients*****with*****clinically significant depressive symptoms (baseline PHQ-9 ≥ 5)**			
Process of care			
Key outcome - components of initial depression care (CIDC): antidepressant prescription and/or mental health referral among participants with baseline PHQ-9 ≥ 10*	X		PQ, PCPQ, MRR
Others			
Antidepressant prescription and/or mental health referral among all sub-study participants*	X		
Follow-up with PCP at an appropriate interval†	X		
Inquiry regarding self-harm/suicidal thoughts	X		
Patient function			
PHQ-8^‡^ score	X	X	PQ
SF-12 Mental Component Summary score		X	
SF-12 Physical Component Summary score		X	
Patient engagement in depression care			
Readiness			PQ
To discuss depression (in general) with PCP	X		
To discuss depression treatment with PCP	X		
Self-efficacy			
For recognizing depression	X	X	
For discussing depression with PCP	X	X	
Provider-patient interaction			PQ, PCPQ, MRR
Discussion of depression	X		
Patient request for depression treatment	X		
Patient perceived depression stigma	X	X	PQ
**Sub-study 2: patients*****without*****clinically significant depressive symptoms (baseline PHQ-9 < 5)**			
Process of care			
Antidepressant prescription (over-treatment)	X		PQ, PCPQ, MRR
Distraction effects			
Index office visit length	X		
Patient request for depression treatment	X		
Physician visit effort	X		
Patient function			
SF-12 Physical Component Summary score (potential toxicity, i.e. reduced function)		X	PQ
Patient perceived depression stigma (potential reduction)	X	X	PQ

* Sub-study 1 primarily powered to examine this outcome; research evidence indicates PHQ-9 scores ≥ 10 are associated with significant life impairment (e.g. reduced functional abilities) and a strong likelihood of clinical depression, while scores of 5–9 are more equivocal in this regard.

^†^ Not an evidence-based element of care, but endorsed in prevailing clinical practice guidelines.

^‡^ Includes all PHQ-9 items except the item concerning self-harm thoughts.

Abbreviations:

*AMEP2*, Activating Messages for Enhancing Primary Care Practice; *MRR*, medical record review; *NA*, not applicable (participants in this sub-study are not followed up); *PCP*, primary care provider; *PCPQ*, PCP questionnaire; *PHQ*, Patient Health Questionnaire; *PQ*, patient questionnaire.

### Participants: setting, eligibility, recruitment and institutional review board requirements

We chose to test the targeted and tailored interventions in clinical settings because they are logistically convenient and permit greater investigator control over the intervention. Additionally, patients who are already seeking care for other reasons are closer to the “decision point” for depression care-seeking, where social marketing interventions are likely to be more effective. Figure 1 illustrates the path patients followed from eligibility screening to 12-week follow up, which is described below.

**Figure 1 F1:**
[figure not shown]
Study design.

Patients and physicians were recruited from primary care clinics affiliated with two large academic medical centers: University of California (UC) Davis and UC San Francisco (UCSF). While the UCSF performance site primarily involved academic primary care clinics, the UC Davis site offered a mix of academic clinics (where full-time faculty and residents share a practice) and urban and suburban primary care network clinics (where most practitioners are full-time primary care clinicians). Additional performance sites were added to contribute to the diversity of the patient sample; these included adult primary care clinics affiliated with Kaiser Permanente, the United States Department of Veterans Affairs (VA) Northern California Health System, and the Sutter Medical Group (all in Sacramento), plus the San Francisco VA Medical Center.

The AMEP2 study obtained local ethics committee review and approval by the institutional review board (IRB) of record for each study site, including the UC Davis Institutional Review Board (Protocol # 214193); the UCSF Human Research Protection Program Committee on Human Research (Reference #041503, which also covers the San Francisco VA); the IRB/Human Studies Subcommittee of the Department of VA, Northern California Health System (Protocol # 10-10-00600); the Kaiser Permanente Northern California IRB and the Sutter Health Central Area IRB (Reference #226984). The Kaiser Permanente and UC Davis institutional review boards permitted research assistants (RAs) to call patients directly from the appointment lists of consented doctors. At the Sutter Medical Group, the VA sites, and UCSF, the IRBs required that RAs first introduce the study with a letter from the performance site’s principal investigator to prospective research subjects who were scheduled for an upcoming primary care visit. Patients receiving the letter were invited to opt out of the study by telephone within 7 days of receiving the letter. Patients who chose not to opt out were called by RAs to assess interest and eligibility to participate in the study.

Primary care (internal medicine and family practice) physicians and residents in their second and third years of training were eligible for the study and were recruited through email announcements and in-person presentations. Physicians were asked to allow the research team to enroll up to 12 of their patients; they were also asked to complete a brief post-visit questionnaire about the content of the index visit for each patient participating in the study and ideally agree to have the visit audio recorded. Physicians who signed informed consent generally provided blanket consent for their patients to be contacted regarding the study. One physician participant asked to screen all her prospective research subjects before research assistants (RAs) initiated contact.

### Procedures for telephone screening interview for eligibility and sampling of patients

Primary screening for patient eligibility was conducted using a short telephone interview administered one to two weeks before the patient’s next scheduled primary care visit. Patient eligibility was based on: the ability to read and understand English; the ability to use a computer program, and the patient’s self-report that he/she was not currently taking medication for depression. In order to enrich the sample with more severely depressed patients, all patients with a PHQ-8 score of 10 or more were invited to participate. For those patients having a PHQ-8 score of less than 10, a custom programmed computer software application was used to randomly sample patients for inclusion in the study. Patients were sampled independently with varying probabilities (Poisson sampling) according to their PHQ-8 score category and the calendar time of screening, with the sampling probabilities updated occasionally to help ensure that the study would accrue the target total sample of 308 in the non-depressed group. Eligible patients who verbally agreed to participate in the study at the end of the screening interview were invited to a research appointment on the day of their scheduled primary care visit.

### Procedures on Day of office visit: prior to randomization

Patients were asked to meet the RA in their primary care physician’s waiting room one hour before their scheduled visit. Upon meeting the patient, the RA accompanied the patient to a private room or a quiet alcove of the waiting room to conduct informed consent and complete the intervention.

Informed consent was obtained in-person by the RA during the research appointment. RAs explained all research procedures, including the use of computerized surveys before and immediately after the doctor’s visit, the importance of audio recording the visit, the possibility of being contacted for a 12-week follow-up interview, and procedures for obtaining study payment (a $20 gift card at the index visit and a $10 gift card for the 12 week follow-up) . Patients had to provide informed consent and sign a Health Insurance Portability and Accountability Act (HIPAA) release, thereby allowing the research team access to the primary care physician’s progress note for the visit, in order to continue with the study. Patients were also asked to provide their consent to have their doctor visit audio recorded when the physician provided prior consent for this component of the study, which was presented as being “optional” to both physicians and patients. At least one audio recording was collected from 81 of the 135 physicians (60%) participating in our study. Patients who successfully completed the informed consent process were logged on to a tablet PC for randomization and intervention assignment. When the intervention was conducted in a waiting room, patients were provided with a headset to keep the multi-media computer intervention private and to minimize distractions associated with busy waiting rooms.

